#### Statistical analysis

Quantitative analysis will focus on descriptive summaries. For each group the numbers of individuals approached, randomly assigned, receiving intended treatment, completing the study protocol, and providing outcome data will be summarised.  The number of individuals withdrawing from the intervention and/or the trial, and where available, the reasons for withdrawal, will be summarised by trial arm.  For each data collection point the number of non-responders will be calculated and attendance rates compared.  A CONSORT diagram will be provided to display the flow of participants through the study.

### Analysis of economic and quality of life data

The completeness of returned HRQoL and health care utilisation data will be assessed to inform an economic evaluation alongside a full RCT. Returned service use data will be used to revise questionnaires used in a full trial.

Costs of delivering the interventions will be measured by recording the resources utilised in the delivery of the IMPACT 4S intervention (including behavioural support, CO monitoring and feedback, pharmacotherapy, costs for telephone/remote modes, client information-sheets, advisor’s resource for clients’ records and information leaflet costs) and BA (including the counselling and information leaflet). We will also capture the costs of intervention setup, training, as well as ongoing support and supervision of the personnel delivering the intervention. We will capture participant travel costs and travel time to attend intervention sessions, including whether they were accompanied by carers/families, and the related travel and time costs. For each trial arm, the costs of providing the intervention (including set-up, training, and ongoing support and supervision) will be calculated. Given the sample size, we would not conduct a full economic evaluation at this stage, as a much larger RCT is needed to undertake a cost-effectiveness analysis.

**Suicidality:** If during the recruitment, assessments or intervention delivery, the participant expresses thoughts, feelings or other or signs that indicate threat to his or her life, appropriate action will be taken to handle it. SoPs for dealing with low, medium and high risk would be as follows:

***Low risk:*** The patients with Low risk will be recommended for Tele follow up (IVRS- Interactive voice response system) and will be linked with the concerned unit for needed intervention

***Medium and High risk:*** The patient with medium and high risk will be advised to get admitted in emergency. If the patient permits/consents family members will be informed

about the patients heightened risk, information on monitoring and treatment.

## PROCESS EVALUATION

The process evaluation will be informed by the Medical Research Council guidance for process evaluation^62^ which identifies three components: implementation, mechanisms of impact and context.

### Implementation (feasibility) and context

Once delivery of the IMPACT 4S and brief advice interventions are completed, the psychology graduates and social workers who delivered these interventions will be interviewed to explore their experiences, including the acceptability of the interventions and the barriers and drivers to delivery including contextual factors such as the health facility environment.

### Implementation (fidelity)

Fidelity to delivering the behavioural support and brief advice interventions will be assessed using a fidelity index. This consists of two sub-indices: The Adherence Index that assesses adherence to the intervention activities; and the Quality Index, that assesses competence with which the intervention was delivered. Both indices are scored on a three-point Likert scale (0=not implemented, 1=partially implemented and 2=fully implemented).

All counselling sessions will be audio-recorded. The researchers will perform the fidelity check by reviewing the audio-recording the counselling sessions of a randomly selected 10% of participants per trial arm. For the IMPACT 4S group, they will ensure a mix of participants who completed/did not complete all their sessions.

### Mechanisms of impact (acceptability and mediators)

To capture the views and experiences of participants, all participants will complete a short questionnaire at the end of the intervention, as part of the three month follow up. Depending on their trial arm allocation, this will explore which components of the brief advice/ IMPACT 4S intervention they engaged with, the acceptability of each session including the CO monitoring, their use of pharmacotherapies and perceived impact of the interventions on their smoking behaviour. Participants in both trial arms will complete some acceptability questions on trial processes.

A purposive sample of participants in each country (12-16 in the IMPACT 4S arm, 4-8 in the BA arm), reflecting a mix of men and women who have/have not quit smoking will be interviewed to collect more in-depth feedback. For the IMPACT 4S intervention, this will be 3-4 participants each for men who quit, women who quit, men who did not quit, women who did not quit; whilst for BA it will be 1-2 participants for each group.

Data on potential mediators likely to influence the mechanism of impact of the intervention ingredients on cessation will be collected at all follow-ups (*see 5.15.6*).

All interviews will be conducted face-to-face using a topic guide and digitally audio-recorded. They will be about an hour long. A hermeneutics approach, which encourages participants to discuss features of the intervention to elicit data on their experience and evaluation of its delivery/receipt will be used.^63^

Participants will provide written informed consent for these interviews, separate from the trial, after having received enough information for this study component and their questions being answered. The consent procedures will be the same as for the trial.

The quantitative data from the fidelity index and questionnaire will be analysed using descriptive statistics, including means and standard deviation for continuous variables, and absolute and relative frequencies for categorical variables. Interviews will be transcribed verbatim and translated into English and analysed using the Framework Approach^64^ which is designed to address applied programme and policy-related questions. NVivo 11 software will aid data handling. Integration of interview findings with respective questionnaire data will be done using a ‘triangulation protocol’.^65^

## DATA MANAGEMENT

### Data handling and storage

The researchers will assure that participants’ anonymity is maintained and that their identities are protected from unauthorised parties. Participants will be assigned unique study IDs and these will be used on all data collection questionnaires, tools and other study records; participants will not be identified by their names. The country coordinating centres will keep and maintain any study logs (including screening and enrolment logs) showing study IDs, names, age and other identifiable information of the participants securely under password protection (for electronic records) or lock and key (if hard copies). The study sites have filing cabinets with lock and key for data storage. All consent forms will be secured safely in a separate compartment of this cabinet. Study information (including consent forms, screening and enrolment data, baseline and follow-up data, audio-recordings and transcripts) will only be accessed by researchers, and will not be released without written permission, except as necessary for monitoring by study monitors or regulatory bodies, for example if the study is audited. Encrypted data transfer between the study sites and the University of York will be via secure Drop-off services available through the University of York.

### Archiving

At the end of the study, data will be securely archived by the University of York, NIMHANS and IoP, as appropriate, for 10 years.

## DATA MONITORING

Data will be monitored for quality and completeness by a delegated researcher at the study sites, followed by a second check by the study Research Fellow at the University of York using verification, validation and checking processes. We will follow the York Trials Unit’s guidance regarding processes for data monitoring. Missing data will be pursued until study end unless they are data obtained by participant contact and this would cause distress. Data will be reported to the Independent Trial Steering Committee (ITSC) and Data Monitoring and Ethics Committee (DMEC) as required.

## OTHER ETHICAL CONSIDERATIONS

The study will commence following a formal ethics review and approval from the University of York’s Health Sciences Research Governance Committee. Ethics applications will also be submitted to the National (Indian Council of Medical Research, National Bioethics Committee Pakistan) and where required, institutional (such as the Ethics Committee (Behavioural Sciences Division), NIMHANS, Bangalore, India) levels in all participating India and Pakistan.

This study is part of a programme of research in South Asia called IMPACT. Approvals will also be sought collectively for the IMPACT studies from each administrative site in each participating country prior to commencement of IMPACT’s research activities.

The study will adhere to the fundamental principles of human rights and dignity laid down in the Declaration of Helsinki. Every possible effort will be made to uphold the principles of autonomy, justice, beneficence and non-maleficence in the design and conduct of the study. Firstly, the eligibility criteria are broad and inclusive to ensure inclusion of groups that may benefit from the trial. There will be no monetary benefits for recruited trial participants. Individuals will provide an informed consent and will have the right to discontinue participation at any point in the study. During study visits and data collection, efforts to minimize inconvenience and burden to participants will be maximised including seeking prior appointments for home visits if these are necessary. Enrolled participants will always be assured of complete confidentiality of their data; participant names will not be used.

## ADVERSE EVENTS

The principles of ICH GCP require that both investigators and sponsors follow specific procedures when notifying and reporting adverse events or reactions in clinical trials. This section of the protocol describes the potential adverse events (AEs), adverse event monitoring during the trial, definitions of adverse events and reporting procedures.

### Description of potential adverse events

Below we describe the potential AEs from each of the components of the study.

#### Feasibility trial

Research procedures

Our procedures for questionnaire completion involve interviewer-administration where participants will be asked questions that they might find uncomfortable to answer. All our study procedures will be conducted by experienced and appropriately qualified researchers who are trained on privacy and confidentiality. These researcher will provide assurance to participants that any information provided will be kept confidential, and study data will only contain thier study ID and not participant names or any other information that might be used to identify the respondents. Whilst answering all questions would really benefit the study achieve its aims and objectives, there might be questions that participants might feel strongly that they do not want to answer. We will advise them to let the researcher know so that they do not continue to ask them those specific questions. It is possible that some of the questions might cause distress. The participants will be advised to ask the researcher to take a break or stop the interview all together. The researcher will also seek help from clinic staff (e.g. counsellors) on the participant’s behalf if the participant feels they need such help.

Trial interventions

Behavioural support, information leaflet and CO monitoring: These are low risk interventions. However, in some circumstances the information or feedback provided might cause anxiety and distress for participants. In such circumstances, researcher will seek help from clinic staff (e.g. counsellors) on the participant’s behalf if the participant feels they need such help.

Pharmacological support: Bupropion and nicotine replacement therapies are generally safe medicines, and have very few side effects. For bupropion, these include nausea, stomach ache, dryness of mouth, sleeplessness, mood changes, appetite changes and headache. We will seek advice from the participant’s mental health care team on whether they can take bupropion before we prescribe this for them. Nicotine gum gives small amounts of nicotine through a gum; and the patches will deliver it through the skin. While the participant will continue to get some nicotine in their system, they will not be exposed to any of the other harmful chemicals that are found in tobacco. Some of the side effects from nicotine gum are mouth or throat sores, bad aftertaste, problems with existing dental work, nausea, jaw pain and racing heartbeat. Some of the side effects of nicotine patches are skin irritation, itching, dizziness, headache, racing heartbeat and nausea. We will advise participants about these potential side effects, and to contact the study team as soon as possible if they suffer from any side effects (serious or otherwise), for us to advise them on what to do. If the side effect(s) are serious enough and the participant feels they need immediate medical attention, they will be informed that they should seek medical help in such circumstances and inform the medical team about their participation in the study and the medicines they are taking as part of the study, and also other medicines that they might be taking.

#### Process evaluation

Our process evaluation component mainly involves interviews with participants and the psychology graduates/social workers that will deliver the interventions to explore their experiences with the intervention. Although we do not foresee any concerning harms from this, our researchers will receive training in supporting interviewees in case of any distress; a break may be taken in the interview, help may be sought from clinic staff (e.g. counsellors) or the interview can be resumed at a later date or cancelled altogether.

### Adverse event monitoring

AEs will be assessed at each counselling session and at the face-to-face follow-up visits, and their potential association with study interventions or procedures ascertained. The researcher conducting the counselling session or follow-up visit assessments will record all directly observed AEs and all AEs reported by the study participant. An adverse events review checklist will be developed to be used at each visit / session to explicitly prompt for symptoms relating to possible nicotine replacement therapy or bupropion related toxicities. This way we will be able to address any AEs or concerns that the participants might have.

In the context of this study, it is very unlikely that any AEs would be related to the behavioural support within the IMPACT 4S intervention nor the BA as they are educational and motivational intervention and that are not harmful. The research procedures are also very low risk. Nevertheless, there is a potential for AEs due to the pharmacotherapies (nicotine replacement therapy or bupropion). AEs will be reported on the AE form. Serious adverse events will be defined according to ICH GCP, and will be reported to the respective country coordinating centres according to the agreed timelines.

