The behavioural support will include BCTs chosen from a BCT taxonomy from a European context as no similar taxonomy has yet been developed for smoking cessation in LMICs^40^ and will also include BCT previously used for smoking cessation India.^41^ The BCTs will include goal setting, problem solving, social support, information about health consequences and adding objects to the environment. Participants will be encouraged to: (1) reduce smoking to quit, (2) set their own quit dates and (3) make several attempts to quit if their initial attempt fails. The IMPACT 4S intervention has been designed for either face-to-face, remote, or a combination of both face-to-face and remote sessions, to allow adaptation to practical feasibility and participants’ preferences. Remote sessions can be delivered using a number of different options such as telephone or video platforms (e.g. What’s App, messenger, Zoom etc.). The IMPACT 4S Intervention comprises of up to 15 one-to-one counselling sessions, each lasting between 15-40 minutes duration. Each session will be delivered by trained psychology graduates in Pakistan and psychology graduates and social workers in India. Delivery will be facilitated through the use of an intervention manual/guide, a flipbook containing key messages on how to quit smoking, and participants’ resource material. In the case of face-to-face delivery, the manual or flipbook will help intervention delivery staff to deliver messages via photo images on the front of the slides and text on the back of slides and same messages will be reiterated in posters and leaflets. This type of intervention delivery involving face-to-face mode is familiar for health and social workers as well and counsellors in these settings and has been found feasible and acceptable in the TB & Tobacco trial being conducted in Bangladesh and Pakistan.^34^ In order to facilitate the remote delivery of the intervention: 1) an adapted remote intervention manual will be use to deliver the intervention in a way that is consistent with face-to-face sessions; and 2) participants will be supplied with a set of seven-colour coded information sheets in advance that will provide information for each session, including any relevant ‘tasks’ that the participant will be required to complete for each session (e.g. smoking diary, reviewing the checklist for quit day and noting down reasons for stopping.

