Participants in this arm will also be offered pharmacological support to aid smoking cessation (nicotine replacement therapy or bupropion either separately or ideally in combination). Pharmacotherapies will be provided for a minimum period of three months. Participants who opt to take bupropion will be referred to their medical doctor for assessing suitability of prescribing bupropion. Participants will be offered sustained-release bupropion, 150 mg/d for the first week and 300 mg/d thereafter. The pharmacological support will be provided for free within the trial. The participants will be scheduled for prescribed medication collection during their face-to-face sessions. In case of changes in mobility restrictions as complying to the local government guideline for managing the upcoming Covid-19 pandemic situation, all scheduled prescribed medication shall be dispatched or personally delivered to the participants’ residential address by post or by research assistants, respectively. Medications for one month will be handed over to them personally by the research staff. An excel sheet log will be maintained for the dispensation, consumption, replenishing and monitoring of Bupropion/Nicotine gums for all the participants who choose pharmacotherapy. The excel sheet log will be filled for medication related details by the research assistants delivering the 4S intervention to the participants and will be centrally managed by the trial manager. The trial manager and the research assistant will monitor the excel sheet log daily to verify if patients would be close to finishing their one-month’s stock of Bupropion/Nicotine gums and need replenishment of a fresh stock. Patient participants who are close to finishing their medications will be given a telephone call one week in advance and asked to visit the NIMHANS campus again to collect the smoking cessation medication for another month; in case, they cannot come to collect the medications, the medications will be personally delivered to the patients. The medications will be provided for a period of three months in total. If there is requirement of bupropion/nicotine gums beyond three months, they will be referred to the treating clinical unit. The patients will be reimbursed the travel costs and compensated for the time they spent in procuring the medication from NIMHANS. The patients will be educated about the correct dosage and method of use, side effects of bupropion/nicotine gums along with an information leaflet on the medications and will be provided contact details to report side effects and for advice. A referral to emergency services will be facilitated in case of a serious adverse event. The participants will be informed to keep the medications in their safe custody and out of reach of children. bupropion/nicotine gums are medications that are routinely prescribed for smoking cessation, including for persons with severe mental illness. Suicide risk assessment will be carried out during the sessions in the intervention arm. Consent to contact family members in case the patient is not reachable on telephone will be sought to mitigate any risks associated with overdose. In case of overdose, a referral to the nearest emergency services will be facilitated. The adherence to medications will be documented in the counsellor’s record book in each session.

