### Baseline and follow-up data collection

Data will be measured and collected from participants and carers face-to-face or remotely at baseline, one, three and six months. Data will be either be entered in paper format or directly into an online survey tool (Qualtrics)^46^ using tablets.

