**Table 1. Baseline and follow-up measurement**

| **Measurement** | **Baseline** | **1 month**  **(Follow-up 1)** | **3 months**  **(Follow-up 2)** | **6 months**  **(Follow-up 3)** |
| --- | --- | --- | --- | --- |
| Demographic data | X |  |  |  |
| Preference for mode of intervention delivery | X |  |  |  |
| Carers/ family members’ involvement | X |  |  |  |
| Details of psychiatric medication | X | X | X | X |
| Smoking status | X | X | X | X |
| Nicotine dependence and urge to smoke | X | X | X | X |
| Quitting smoking intentions, motivations and behaviours | X | X | X | X |
| Mediators of smoking cessation | X |  | X | X |
| Health-related quality of life | X |  | X | X |
| Mental and physical health | X |  | X | X |
| Health services use | X |  | X | X |
| Physical body measurements (height; weight) | X |  | X | X |
| Smoking cessation pharmacotherapy adherence |  | X | X | X |
| Process evaluation questionnaire and interviews |  |  | X |  |

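### AE assessment at follow-up is tied to face-to-face visits although follow-up may be remote, so adverse event data can depend on visit mode

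*Protocol*

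**What the plan says.** Section 10.2 (Adverse event monitoring) sets the schedule in its first sentence: "AEs will be assessed at each counselling session and at the face-to-face follow-up visits". The same paragraph continues without any limit on mode: "The researcher conducting the counselling session or follow-up visit assessments will record all directly observed AEs and all AEs reported by the study participant", and "An adverse events review checklist will be developed to be used at each visit / session".

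Section 5.15 (Baseline and follow-up data collection) allows either mode: "Data will be measured and collected from participants and carers face-to-face or remotely at baseline, one, three and six months". Table 1 in section 5.16 lists what is measured at each time point. It has a row for adherence to the smoking cessation drugs but none for adverse events or suicide risk.

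Section 5.1 (Arm 2: IMPACT 4S intervention) says the intervention "comprises of up to 15 one-to-one counselling sessions", in person or remote, and sets no minimum. Trial medication is supplied a month at a time for three months. Collection is planned at face-to-face sessions. Posting or delivery is the fallback under mobility restrictions, and personal delivery is the fallback when the participant cannot come. Before each refill, "Patient participants who are close to finishing their medications will be given a telephone call one week in advance". On suicide risk the section says "Suicide risk assessment will be carried out during the sessions in the intervention arm". The suicidality paragraph in section 5.19 is wider, covering recruitment and assessments as well as intervention delivery, but it acts only when a participant shows signs of risk.

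**The concern.** The sentence that fixes when adverse events are assessed names one mode of follow-up, while the follow-up section allows two. A site that follows the literal rule would complete a remote follow-up, ask how many doses were taken, and not be required to ask about harm. A site that follows the later wording would use the checklist. Two sites could therefore collect safety data differently under one protocol.

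Section 10.2 itself places the potential for adverse events in the drug treatment. The scheduled contacts that remain for remotely followed participants are the counselling sessions, and attendance at those is one of the trial's feasibility questions (primary outcome 5). The participants with the fewest AE checks would thus be those who engage least. A low event count could then reflect how often people were asked rather than how well they tolerated treatment, and tolerability is part of what this pilot passes on to a definitive trial.

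**Working it through.** The protocol gives no figure on this point to reproduce. The check sets the passages side by side and counts contacts.

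**Inputs**
- IMPACT 4S sessions: up to 15 (section 5.1).
- Brief advice: one contact (section 5.1), described as a counselling session in the Summary.
- Follow-ups: three, at months 1, 3 and 6 (section 5.16).
- Enrolment: 172, allocated 1:1 (sections 5.18 and 5), so 172 / 2 = 86 per arm.
- Supply: three one-month supplies, so two refills, each preceded by a call (section 5.1). The refill procedure is written around the Bangalore campus; I assume it applies at both sites.
- Share of follow-ups held remotely: not given. I use 10%, 30% and 50% as assumptions.

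**Step 1. Scheduled AE contacts per participant, literal first sentence of section 10.2**

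| Follow-up mode | IMPACT 4S | Brief advice |
| --- | --- | --- |
| All face-to-face | up to 15 + 3 = 18 | 1 + 3 = 4 |
| All remote | up to 15 + 0 = 15 | 1 + 0 = 1 |
| All remote, no session attended | 0 | not applicable |

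**Step 2. Planned contacts in months 0 to 3 for an IMPACT 4S participant who attends no sessions, has medication delivered and is followed remotely**
- Two refill calls plus the one- and three-month follow-ups: 2 + 2 = 4 contacts.
- Literal reading: 0 of 4 must include an AE check.
- Wider reading, with the checklist at every visit in any mode: 2 of 4. The refill calls are still not covered.

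**Step 3. Follow-ups that fall during drug supply**
- Supply ends at three months, so months 1 and 3 count and month 6 does not.
- Upper bound: 86 x 2 = 172 follow-ups, before attrition. That this equals the enrolment total is coincidence.
- 172 x 0.10 = 17.2, about 17.
- 172 x 0.30 = 51.6, about 52.
- 172 x 0.50 = 86.

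**Step 4. Does the protocol settle the matter elsewhere?** Where remote working removes a measurement, section 5.15 says so, for breath CO and for height and weight. It makes no such statement for adverse events, in either direction. Table 1 does not help, because it has no AE row.

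**The case against.** The best defence is that the later sentences of section 10.2 already cover remote visits. The researcher doing the follow-up assessment records reported events, and the checklist is for every visit or session. This stands in part. A reader might infer that the protocol deliberately excludes remote follow-ups from AE assessment; the documents do not support that, because the paragraph disagrees with itself.

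A reader might also infer that drug supply runs separately from the sessions. It does not: collection is planned at face-to-face sessions, delivery is a fallback, and the staff delivering the intervention keep the medication log. What remains is that section 5.1 makes neither delivery nor the refill call depend on a session or an AE question.

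Nor does missing some sessions leave a participant unchecked, since every attended session, in person or remote, carries an AE assessment. A complete gap needs near-total non-attendance, delivered medication, remote follow-up and the literal reading together.

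Other contacts exist. Participants are told to record and report side effects (sections 10.1 and 10.4). Researchers keep in telephone contact (5.13). The suicidality procedure applies at assessments (5.19). The MPSS is taken at one, three and six months, and the PHQ-9 at three and six (5.15). These rely on the participant, react to expressed risk, serve retention, or score symptoms for another purpose. None is a scheduled AE check.

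Finally, Table 2 defines an adverse event by receipt of an investigational medicinal product. The contrast between arms therefore matters only if events are also tabulated for brief advice.

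**Conclusion.** The inconsistency is real and should be corrected. On the literal schedule, AE ascertainment depends on visit mode, session attendance and arm: up to 18 versus 4 contacts face-to-face, up to 15 versus 1 remote. At most 172 follow-ups fall during drug supply, of which about 17, 52 or 86 would lack an AE check at assumed remote shares of 10%, 30% or 50%. These are upper bounds: drug treatment is offered rather than compulsory, the sample-size section expects 30% attrition, those who attend sessions are checked there, and the wider reading of section 10.2 would bring the number to zero.

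A reader might multiply all 172 participants by three visits to get 516 affected follow-ups. That figure does not measure unmonitored exposure to trial drug, because it includes the brief advice arm and the month-six visit, after trial supply has ended.

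It would also go too far to say that suicide risk is unmonitored outside sessions. Scheduled assessment is named only for intervention-arm sessions, but the section 5.19 procedure reaches assessments as well.

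**What to change.** Three changes of wording:

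- In section 10.2, delete *face-to-face* from the first sentence, so that the AE checklist is used at every one-, three- and six-month follow-up in either mode.
- Add an adverse event row to Table 1 at those three time points.
- In section 5.1, state that AE checklist answers are recorded at the replenishment calls already planned, and whether those calls are made at both sites.

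Separately, the sponsor must reconcile the section 5.1 statement on suicide-risk assessment in sessions with the section 5.19 suicidality procedure for participants who do not attend sessions. This review does not propose what the rule should be.

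The cost is a protocol wording change and a few minutes on contacts that already take place. A small downside is that more non-serious events will be recorded. Because sessions still outnumber follow-ups in one arm, any AE table by arm should also show the number of contacts at which events were asked about.
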